#### Bayesian methods

The estimation of the demand model requires an assumption of prior distributions of the model parameters. As is standard in the literature, normal distributions will be assumed for the model parameters, chosen partially due to their computational aspects. Prior means for the model parameters informing the PEs, {β_*i*_} and {γ_ij_}, will be specified with the help of two matrices of PE estimates from BODE^3^ [40] and SPEND [29], ∈ _ij_^BODE3^ and ∈ _ij_^SPEND^, respectively. The PE matrix from BODE^3^ consisted of 22 food categories with PE values adapted from the literature for developed countries. The PE matrix from SPEND was estimated from the Household Economic Survey data in New Zealand for 24 food categories.

Equation (2) will be used in connection with the PE matrices to construct priors for demand equation parameters: α_i_, γ_ij_ and β_i_ in Eq. (1). Since the number of parameters to calculate is larger than the number of prior PEs, we will also use a prior simulation approach in connection with additional assumptions to set reasonable prior means for all parameters.

We will then develop an algorithm that accommodates these priors and zero expenditures to estimate a demand system using an AIDS model as detailed from Eqs. (1, 2 and 3).

Steps to estimate the Bayesian AIDS model include:Specify functional form for the demand model, which is an AIDS equation system.Convert prior PE matrices to prior mean parameters in the demand model.Use Monte Carlo simulation to draw values for the prior parameters from specified distributions.Use Bayesian approach to combine the prior information for the parameters with the data from the VS experiment to obtain estimates for these parameters based on their posterior distributions.Calculate PE values from the posterior distributions of parameters.

#### Price elasticity estimation

As part of the Bayesian model estimation we will compute point and interval estimates for PEs, both own-PEs and cross-PEs by income level and ethnicity. We will also calculate compensated/uncompensated PEs, and conditional/unconditional PEs for a complete food demand system. We will estimate a standard PE matrix as in the literature; PE matrices by specific fiscal policy; and a PE matrix for combined fiscal policy analyses in this project.

### Step 4: estimate health impacts from food taxes and subsidies

Finally, in Step 4, we will run disease simulation models (MSLT simulation models) with the two alternative methods of capturing dietary change following taxes and subsidies, namely:Directly inputting the average amount of each food product purchased per adult in the VS (Step 2) for each policy option, which then flows into changes in dietary risk factors.Using the PEs from Step 3, and then merging with a price change through to changes in food purchases and then the same flow through dietary risk factors.

The main output of the MSLT will be QALYs gained and net health system costs for the five selected fiscal policy options, for interventions (outlined taxes and subsidies) and business-as-usual (BAU, no tax or subsidy) scenarios for the entire New Zealand population alive in 2011, simulated out until death. This BODE^3^ DIET MSLT uses projected all-cause mortality and morbidity rates by sex and age for Māori and non-Māori in a ‘main’ lifetable. Running alongside this main lifetable are 17 diet-related disease lifetables, where proportions of the population simultaneously reside: coronary heart disease, stroke, type 2 diabetes, osteoarthritis, and multiple cancers (oesophageal, pancreatic, kidney, colorectal, endometrial, lung, thyroid, liver, stomach, head and neck, gallbladder, ovarian and breast). The proportion of the New Zealand population in each disease lifetable is a function of the disease incidence, case-fatality and remission (in cancers only).

The intervention effect is captured through changes in grams of food consumed between the BAU and intervention scenarios (either through directly inputting the average amount of each food product purchased per adult in the VS or through PEs, as outlined above). This will then be converted into a change in energy, fruit, vegetables, SSBs and sodium intake and the percentage of total energy from polyunsaturated fat. Energy intake will be used to calculate changes in body mass index. The change in these risk factors will then be combined with relative risks for the associations with the various diseases through population impact fractions (PIFs) that alter the incidence of the diet-related diseases.

Each diet-related disease has incidence, prevalence and case-fatality specified by each sex, age and ethnic group (Māori and Non Māori) in 2011. Remission rates were specified for cancers, but set to zero for coronary heart disease, stroke, type 2 diabetes and osteoarthritis as remission for these diseases is generally unlikely. Sex, ethnic and age-specific morbidity will be calculated for each disease using the years of life lived with disability (YLDs) from the New Zealand Burden of Disease [41], which in turn were estimated using disability weights from the Global Burden of Disease 2010 Study [42].

The net health system cost (NZD) will be the net of the intervention cost (i.e., the cost of a new law in New Zealand requiring the tax intervention [43] or paying for the subsidy programme) and any difference in projected future health system expenditure resulting from changes in disease incidence due to the interventions. Sex and age-specific health system costs (2011 NZD), will be calculated using individually linked data for publicly funded (and some privately funded) health events. Building on an existing framework for calculating the timing of health system costs [44], everyone in the model will be assigned a sex and age-specific annual cost of a citizen without a diet-related disease and not in the last six months of their life. Additional disease-specific excess costs will be assigned to people in the first year of diagnosis, last six months of life if dying of the given disease, and otherwise prevalent cases of each disease. Costs will be modelled over the lifetime of the cohort, including costs related to the diet-related diseases modelled and those not related to these diseases. This means that increased longevity due to dietary interventions contributes to increased health system costs for some cohort members.

The MSLT model is a Microsoft Excel based macro-simulation model using an Ersatz add-in to run the Monte Carlo simulations 2000 or more times. Each of these simulations involves a random draw from the probability density function about the parameters specified with uncertainty in the model. This results in central estimates for QALYs and costs with associated uncertainty intervals.

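### As described, the Step 4 cost rule gives an end-of-life cost only to deaths from the 17 modelled diseases, which biases net health system cost toward larger savings for deaths shifted to other causes

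*Protocol article*

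**What the plan says.** The section on Step 4 (estimating health impacts) builds health system cost from two parts.

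- **Background cost.** Everyone is assigned a sex- and age-specific "annual cost of a citizen without a diet-related disease and not in the last six months of their life".
- **Disease excess.** "Additional disease-specific excess costs will be assigned to people in the first year of diagnosis", and also in the "last six months of life if dying of the given disease, and otherwise prevalent cases of each disease".

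Two further sentences bear on the point. Lifetime costs are counted, "including costs related to the diet-related diseases modelled and those not related to these diseases", and "increased longevity due to dietary interventions contributes to increased health system costs for some cohort members".

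On the model's structure, results are produced "for the entire New Zealand population alive in 2011, simulated out until death". "Running alongside this main lifetable are 17 diet-related disease lifetables", and the policies act through "population impact fractions (PIFs) that alter the incidence of the diet-related diseases".

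**The concern.** Both limits are written into the rule: the background cost shuts out the last six months of life, and the end-of-life excess is tied to dying of a modelled disease. A person who dies of something else is charged the background rate up to death, plus the prevalent-case excess if he or she has a modelled disease, but nothing for the process of dying.

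This would not matter if it cancelled between the business-as-usual and intervention runs. It does not cancel, because the intervention itself changes the mix of causes of death. Everyone in the cohort dies in both runs, so over the lifetime each net modelled-disease death averted is matched by one additional death from another cause. The rule takes an end-of-life cost away for the first and adds none for the second. The years gained in between are charged, but at the rate for people who are not dying.

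Net health system cost is part of the third main outcome (outcome C) and a main output of the life-table model. The error favours any policy that averts modelled-disease deaths.

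**Working it through.** The article gives no end-of-life cost, discount rate, number of averted deaths or net cost, so there is no figure of its own to reproduce. The check is an identity per averted modelled-disease death, followed by illustrative values.

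**Inputs from the article (Step 4):** the background cost excludes the last six months; the end-of-life excess applies to modelled-disease deaths only; there are 17 modelled diseases (4 named conditions plus 13 cancers, which does add up); the cohort is followed to death.

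**Assumed quantities:**
- *C*: end-of-life excess for a modelled-disease death
- *k*: end-of-life excess for another cause, as a multiple of *C*
- *m*: share of those whose modelled-disease death is averted who later die of a modelled disease anyway
- *v* = (1 + *r*)^(−*T*): discount factor at rate *r* over a delay of *T* years

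**Formulas:**
- Credit under the written rule: *C*(1 − *mv*)
- Credit if all deaths are costed: *C*(1 − *mv* − (1 − *m*)*kv*)
- Overstatement: (1 − *m*)*kvC*

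The overstatement is positive whenever *m* < 1 and *k* > 0, and zero if *m* = 1 or *k* = 0.

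**Worked case.** *r* = 3%, *T* = 20, *m* = 0.5, *k* = 0.5. Then *v* = 1.03^(−20) = 0.554. The written rule credits 1 − 0.5 × 0.554 = 0.723*C*. The overstatement is 0.5 × 0.5 × 0.554 = 0.138*C*. The complete rule credits 0.723 − 0.138 = 0.585*C*, and the ratio is 0.723/0.585 = 1.2.

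| *r* | *T* (years) | *m* | *k* | Written rule | All deaths costed | Overstatement | Ratio |
|---|---|---|---|---|---|---|---|
| 3% | 20 | 0.5 | 0.5 | 0.723*C* | 0.585*C* | 0.138*C* | 1.2 |
| 3% | 10 | 0.4 | 0.5 | 0.702*C* | 0.479*C* | 0.223*C* | 1.5 |
| 3% | 10 | 0.4 | 1 | 0.702*C* | 0.256*C* | 0.446*C* | 2.7 |
| 3% | 5 | 0 | 1 | 1.000*C* | 0.137*C* | 0.863*C* | 7.3 |
| 0 | any | 0.4 | 1 | 0.600*C* | 0 | 0.600*C* | not defined |
| 3% | 10 | 1 | any | 0.256*C* | 0.256*C* | 0 | 1.0 |

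**Life-table check.** This used an illustrative two-cause Gompertz cohort from age 40, with modelled diseases causing 30% to 60% of mortality and modelled-disease mortality cut by 5%. Total deaths are identical in the two runs. End-of-life savings per 1000 people, in units of *C*:
- Undiscounted: the written rule credits 10.7 to 12.8. With all deaths costed this becomes 0 (*k* = 1) or 5.3 to 6.4 (*k* = 0.5).
- At 3%: the written rule credits 3.9 to 5.7. With all deaths costed this becomes 1.4 to 2.8 (*k* = 1) or 2.6 to 4.2 (*k* = 0.5).

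Across these settings the share of the credited end-of-life saving that disappears runs from 25% (1.42 of 5.66, at 3%, *k* = 0.5, modelled share 60%) to 100% (undiscounted, *k* = 1).

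**The case against.** The strongest reply is that this reads an omission into a condensed account. The costing takes a few sentences, builds on a cited framework that is not shown, and says that unrelated costs are included. Carving the last six months out of the background cost is just what one would do if a separate end-of-life cost existed for all deaths. This stands in part: the implemented model may already cost deaths from other causes. But the text does more than stay silent. It states to whom the end-of-life excess applies, and the only unrelated cost it describes excludes that period. The sentences on unrelated costs and longevity therefore do not clearly close the gap.

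A reader might also infer that every averted diet-related death is credited with a saving that is merely postponed. The article does not support that. Anyone who later dies of the same or another modelled disease is charged then, and the list includes coronary heart disease, stroke, diabetes and 13 cancers, so this is no marginal group. Nor is the saving wholly postponed unless other causes cost as much at the end of life and costs are not discounted; otherwise part of it is real.

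Finally, the ratios concern one component. Net cost also includes the intervention or subsidy cost, first-year and prevalent-case excesses, and the cost of added years. Nothing in the article shows how much of the total is end-of-life cost, or that every policy yields a net saving; the subsidy's net cost includes paying for the programme. Statements about the size of total savings, or the gaps between policies, would go beyond the document.

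**Conclusion.** The point holds for the rule as described. End-of-life excess attaches to modelled-disease deaths only, so deaths shifted to unmodelled causes lose a cost that is not charged later, and net health system cost is biased toward larger savings or smaller net costs. The direction needs only that some of these people later die of an unmodelled cause and that such deaths carry some end-of-life excess.

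The size is not derivable. The 1.2-fold to 7-fold range for the end-of-life component rests on assumed values of *m*, *k*, the delay and a 3% discount rate; it illustrates and does not bound the error. The share of total net cost is unknown. The matter is of moderate weight and confined to the net-cost part of outcome C.

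**What to change.** In the Step 4 costing paragraph, add a sex- and age-specific last-six-months excess cost for deaths from causes other than the 17 modelled diseases. Estimate it from the same individually linked health-event data, and apply it to those deaths in both the business-as-usual and the intervention runs. If the implemented model already does this, correct the description so that it says so.

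The cost is one more input vector and one more line in a spreadsheet model that the article describes as still under development; no trial data are affected. The downside is that reported savings become smaller.

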## Discussion

The Price ExaM study will provide high-quality evidence on the likely impact of health-related food taxes and subsidies by estimating precise and accurate own-PE and cross-PE values for use in modelling studies.

Good quality own-PEs and cross-PEs are lacking in New Zealand [29] and internationally [13, 15], mostly due to restraints in existing modelling and experimental methods which rely on (often weak) observational data to estimate PEs. Price ExaM aims to overcome these restraints by combining econometric, experimental and simulation modelling methods. To the best of our knowledge, this appears to be the first study globally to use such a combination of methods.

A key feature of Price ExaM is the use of the VS to objectively measure direct responses to price changes for a wide range of food items. Previous studies relied on household economic surveys and/or Food Price Index data which have important limitations including insufficient variation in price; difficulty matching food categories between consumption and price datasets; and statistically imprecise and unstable estimates for foods most relevant to public health research (e.g. cross-PEs between fruit/vegetables and foods high in salt). By exposing 1000 study participants to five different price sets, having different price sets for each participant, and by randomly varying the prices of more than 1400 foods, Price ExaM is likely to generate a uniquely and rich database allowing us to calculate PE values for many different food groupings. Therefore, Price ExaM will not only provide high-quality evidence on pre-selected food tax and subsidy options (e.g., sugar tax, saturated fat tax, salt tax, SSB tax and fruit and vegetable subsidy), but the output can also be used to examine any other fiscal policy impacting on food prices (for example a carbon tax on agricultural emissions), thus offering a unique resource for future research.

The Price ExaM study has the potential to enhance the public health and economic disciplines by introducing internationally novel scientific methods to estimate accurate and precise food PEs. These data will be used to model the potential health and disease impacts and health costs saved of various food pricing policy options. Findings will likely to be highly relevant to inform policy on health-related food taxes and subsidies.

## Trial status

Recruiting.

## Abbreviations

AIDS, almost ideal demand system; BAU, business-as-usual; BODE^3^, burden of disease epidemiology, equity & cost-effectiveness programme; Cross-PEs, cross-price elasticities; FPI, food price index; FV, fruit and vegetables; MSLT, multi-state life-table; Own-PEs, own-price elasticities; PEs, price elasticities; Price ExaM, price experiment and modelling study; QALY, quality-adjusted life-years; RCT, randomised controlled trial; SPEND, strategic pricing: effects on nutrition & disease study; SS, sugar-sweetened; SSB, sugar-sweetened beverages; VS, virtual supermarket

## Appendix 1: procedure to generate price sets for the virtual supermarket

The price sets used in the Virtual Supermarket are generated using the following procedures:

- **Step 1:** We allocate five groups of tax/subsidy policies, with 16 policy subsets, to 5000 price sets. The allocation of tax/subsidy policies are detailed in Appendix 2. In summary, we allocate 60 % (3000) of the price sets to only one policy. Namely, 15 % (750) of the price sets have no policies turned on; 15 % SSB tax; 15 % fruit and vegetables subsidy; 10 % (250) saturated fat tax; 10 % sugar tax; and 10 % salt tax. There are 20 % (1000) of the price sets that have two policies turned on. Finally, there are 5 % (250) of the price sets that have three or more policies turned on. We also create 100 price sets as reserves (e.g. to replace an invalid shop). These sets are randomly drawn from the above 5000 sets.
- **Step 2:** We create random price variations for 1412 food products in the VS. Let’s denote **P** as current food price (sourced from Nutritrack [33] 2011/2012 and online supermarkets, updated for 2014).
  1. Create Ratio1 for each of 21 food categories (e.g. fruit, vegetables, bakery, etc.), randomly selected from a uniform distribution 0.85 to 1.15.
  2. Create Ratio2 for each of 1412 food product, also randomly selected from a uniform distribution 0.85 to 1.15.
  3. Multiply the PxRatio1 × Ratio2 for all 1412 foods to create new prices (**Pnew**). This results in randomly varying prices for all foods, pre-tax/subsidy, ranging from 70 to 130 % of starting P. This allows some correlation within food categories, and independence between food categories.
- **Step 3**: We add tax/subsidy for each of 1412 food products by randomly drawing, without replacement, one of the 5000 policy sets created in Step 1. Depending on which tax/subsidy policy is turned on, the amount of tax/subsidy for each food products will be calculated accordingly (e.g. by multiplying Pnew for SSBs by 1.2 if randomly allocate to policy 1a (Appendix 2 below). That is, denoting **Pnew.ts** as food price after tax/subsidy:

Pnew.ts = Pnew × ∆ tax/subsidy

Note that the ‘∆ tax/subsidy’ is not sampled from a probability distribution, e.g. it is just ‘1.2’ for policy 1a; Step 2 generates random variation.

## Appendix 2

**Table 2 Tab2:** Allocation of tax/subsidy policies to 5000 price sets used in the Virtual Supermarket

Tax/subsidy policies	N where this only policy (% of 5000)	N where they also have another policy turned on (% of 5000)
No tax or subsidy	750 (15.0 %)	750 (15.0 %)
1a. 20 % tax SSB (sugar-sweetened soft drinks only)	100 (2.0 %)	173 (3.5 %)
1b. 40 % tax SSB (sugar-sweetened soft drinks only)	100 (2.0 %)	180 (3.6 %)
1c. 20 % tax SSB+ (sugar-sweetened soft drinks, sugar-sweetened fruit drinks, sugar-sweetened energy drinks, sugar-sweetened sports drinks)	100 (2.0 %)	197 (3.9 %)
1d. 40 % tax SSB+ (sugar-sweetened soft drinks, sugar-sweetened fruit drinks, sugar-sweetened energy drinks, sugar-sweetened sports drinks)	90 (1.8 %)	187 (3.7 %)
1e. 20 % tax SSB++ (sugar-sweetened soft drinks, sugar-sweetened fruit drinks, fruit juices, sugar-sweetened energy drinks, sugar-sweetened sports drinks)	90 (1.8 %)	185 (3.7 %)
1 f. 40 % tax SSB++ (sugar-sweetened soft drinks, sugar-sweetened fruit drinks, fruit juices, sugar-sweetened energy drinks, sugar-sweetened sports drinks)	90 (1.8 %)	175 (3.5 %)
1 g. 20 % tax all soda	90 (1.8 %)	201 (4.0 %)
1 h. 40 % tax all soda	90 (1.8 %)	188 (3.8 %)
2a. 20 % FV subsidy fresh	375 (7.5 %)	764 (15.3 %)
2b. 20 % FV subsidy fresh frozen	375 (7.5 %)	742 (14.8 %)
3a. SAFA tax ($2/100 g)	250 (5.0 %)	516 (10.3 %)
3b. SAFA tax ($4/100 g)	250 (5.0 %)	548 (11.0 %)
4a. Sugar tax ($0.4/100 g)	250 (5.0 %)	443 (8.9 %)
4b. Sugar tax ($0.8/100 g)	250 (5.0 %)	409 (8.2 %)
5a. Salt tax ($0.02/100 g)	250 (5.0 %)	409 (8.2 %)
5b. Salt tax ($0.04/100 g)	250 (5.0 %)	433 (8.7 %)
6. Combination of 2 policies	1000 (20.0 %)	1000 (20.0 %)
7. Combination of 3 or more policies	250 (5.0 %)	250 (5.0 %)
Totals	5000 (100 %)	7750 (155 %)
